11.1.2 Case Report Form (CRF)

In clinical trials, it is necessary to record the specified observations or examination items in the case report form. The case report form includes...

The content must be completely consistent with the original data, and the basis for the results calculated from the original data should be traceable.

When filling out, you must meet the following standards:

(1) Fill in with a black signature pen or black ballpoint pen;

(2) Cases that have already signed the informed consent form and meet the inclusion criteria should fill out the case report form, even if they have not received treatment or are determined to not meet the inclusion criteria after treatment.

(3) When making corrections, the original record must be crossed out with a line (correction fluid or similar cannot be used), but the original record must remain legible. Additionally, the person making the correction must sign at the correction point and indicate the date of the correction.

(4) For unexamined items, it must be marked as "ND (Not Done)".

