11.2 Statistical Analysis

11.2.1 Analysis of Population Definition:

The patients who were enrolled and received treatment constitute the intention-to-treat population (ITT) for this trial. The population and the patients who comply with the requirements of this clinical trial protocol and complete this study constitute the per protocol population (PP). The statistical analysis will use intention-to-treat (ITT) for missing data, comparing the "full analysis set (FAS)" and the "per protocol set (PP)."

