**Appendix 6**

# Table 5 36-Item Short Form Survey

Number： Name：

ID： Tel：

There are a total of 36 questions below, and after each question, there are several answers to choose from. Please fill in the corresponding score in the score column of the table for the answers you think are appropriate.

| Item |  | | | | |  | | | | | |  | | | | | |  | | | | |  | | | Score |
| --- | --- | --- | --- | --- | --- | --- | --- | --- | --- | --- | --- | --- | --- | --- | --- | --- | --- | --- | --- | --- | --- | --- | --- | --- | --- | --- |
| 1. In general, would you say your health is | Excellent | | | | | Very good | | | | | | Good | | | | | | Fair | | | | | Poor | | |  |
|  | 5 | | | | | 4.4 | | | | | | 3.4 | | | | | | 2 | | | | | 1 | | |  |
| 1. **Compared to one year ago**, how would you rate your health in genera **now**? | Much better | | | | | Somewhat better | | | | | | About the same | | | | | | Somewhat worse | | | | | Much worse | | |  |
|  | 1 | | | | | 2 | | | | | | 3 | | | | | | 4 | | | | | 5 | | |  |
| The following items are about activities you might do during a typical day. Does **your health now limit you** in these activities? If so, how much? | | | | | | | | | | | | Yes, limited a lot | | | | Yes, limited a little | | | | | | No, not limited at all | | | |  |
| 1. **Vigorous activities**, such as running, lifting heavy objects, participating in strenuous sports | | | | | | | | | | | | 1 | | | | 2 | | | | | | 3 | | | |  |
| 1. **Moderate activities**, such as moving a table, pushing a vacuum cleaner, bowling, or playing golf | | | | | | | | | | | | 1 | | | | 2 | | | | | | 3 | | | |  |
| 1. Lifting or carrying groceries | | | | | | | | | | | | 1 | | | | 2 | | | | | | 3 | | | |  |
| 1. Climbing **several** flights of stairs | | | | | | | | | | | | 1 | | | | 2 | | | | | | 3 | | | |  |
| 1. Climbing **one** flight of stairs | | | | | | | | | | | | 1 | | | | 2 | | | | | | 3 | | | |  |
| 1. Bending, kneeling, or stooping | | | | | | | | | | | | 1 | | | | 2 | | | | | | 3 | | | |  |
| 1. Walking **more than a mile** | | | | | | | | | | | | 1 | | | | 2 | | | | | | 3 | | | |  |
| 1. Walking **several blocks** | | | | | | | | | | | | 1 | | | | 2 | | | | | | 3 | | | |  |
| 1. Walking **one block** | | | | | | | | | | | | 1 | | | | 2 | | | | | | 3 | | | |  |
| 1. Bathing or dressing yourself | | | | | | | | | | | | 1 | | | | 2 | | | | | | 3 | | | |  |

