| During the **past 4 weeks**, have you had any of the following problems with your work or other regular daily activities **as a result of your physical health**? | | | | | | | | | | | | | | | | | | | No | | | | Yes | | |  |
| 1. Cut down the **amount of time** you spent on work or other activities | | | | | | | | | | | | | | | | | | | 1 | | | | 2 | | |  |
| 1. **Accomplished less** than you would like | | | | | | | | | | | | | | | | | | | 1 | | | | 2 | | |  |
| 1. Were limited in the **kind** of work or other activities | | | | | | | | | | | | | | | | | | | 1 | | | | 2 | | |  |
| 1. Had **difficulty** performing the work or other activities (for example, it took extra effort) | | | | | | | | | | | | | | | | | | | 1 | | | | 2 | | |  |
| During the **past 4 weeks**, have you had any of the following problems with your work or other regular daily activities **as a result of any emotional problems** (such as feeling depressed or anxious)? | | | | | | | | | | | | | | | | | | | No | | | | Yes | | |  |
| 1. Cut down the **amount of time** you spent on work or other activities | | | | | | | | | | | | | | | | | | | 1 | | | | 2 | | |  |
| 1. **Accomplished less** than you would like | | | | | | | | | | | | | | | | | | | 1 | | | | 2 | | |  |
| 19. Didn't do work or other activities as **carefully** as usual | | | | | | | | | | | | | | | | | | | 1 | | | | 2 | | |  |
| 20. During the **past 4 weeks**, to what extent has your physical health or emotional problems interfered with your normal social activities with family, friends, neighbors, or groups? | | | | | Not at all | | | | | Slightly | | | | | Moderately | | | | Quite a bit | | | | Extremely | | |  |
|  |  |  |  |  | 5 | | | | | 4 | | | | | 3 | | | | 2 | | | | 1 | | |  |
| 21.How much **bodily** pain have you had during the **past 4 weeks**? | None | | | Very mild | | | | | | Mild | | | | | Moderate | | | | | Severe | | | | Very severe | |  |
|  | 6 | | | 5.4 | | | | | | 4.2 | | | | | 3.1 | | | | | 2.2 | | | | 1 | |  |
| 22.During the past 4 weeks, how much did pain interfere with your normal work (including both work outside the home and housework)? | | Score selection | | | | | Not at all | | | | A little bit | | | | Moderately | | | | Quite a bit | | | | Extremely | | |  |
|  |  | Answered items 21 | | | | | 6 | | | | 4.75 | | | | 3.5 | | | | 2.25 | | | | 1 | | |  |
|  |  | Unanswered items 21 | | | | | 5 | | | | 4 | | | | 3 | | | | 2 | | | | 1 | | |  |

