| Score conversion = (actual score - lowest score in that aspect) / (highest score in that aspect - lowest score in that aspect) × 100; missing entry scores are replaced by the average score of their respective aspect. | | | | | | | | | | | | | | | | | | | conversion formula | | | | | | | Score conversion |
| Physical Functioning(PF), Consist of items 3-12, | | | | | | | | | | | | | | | | | | | PF=(actual score-10）/20×100 | | | | | | |  |
| Role-Physical(RP) ,Consist of items 13-16, | | | | | | | | | | | | | | | | | | | RP=（actual score-4）/4×100 | | | | | | |  |
| Bodily Pain(BP), Consist of items 21, 22, | | | | | | | | | | | | | | | | | | | BP=（actual score-2）/10×100 | | | | | | |  |
| General Health(GH), Consist of items 1, 33-36, | | | | | | | | | | | | | | | | | | | GH=（actual score-5）/20×100 | | | | | | |  |
| Vitality(VT), Consist of items 23, 27, 29, 31, | | | | | | | | | | | | | | | | | | | VT=（actual score-4）/20×100 | | | | | | |  |
| Social Functioning(SF), Consist of items 20, 32, | | | | | | | | | | | | | | | | | | | SF=（actual score-2）/9×100 | | | | | | |  |
| Role-Emotional(RE), Consist of items 17-19, | | | | | | | | | | | | | | | | | | | RE=（actual score-3）/3×100 | | | | | | |  |
| Mental Health(MH), Consist of items 24-26, 28, 30, | | | | | | | | | | | | | | | | | | | MH=（actual score-5）/25×10 | | | | | | |  |
| Reported Health Transition(HT), Consist of items 2, | | | | | | | | | | | | | | | | | | | HT=（actual score-1）/4×100 | | | | | | |  |
| ReferencesWare, J.E., Jr., & Sherbourne, C.D. “The MOS 36-Item Short-Form Health Survey (SF-36): I. Conceptual Framework and Item Selection,”. Medical Care, 30:473-483, 1992.Hays, R.D., & Shapiro, M.F. “An Overview of Generic Health-Related Quality of Life Measures for HIV Research,” Quality of Life Research. 1:91-97, 1992. Steward, A.L., Sherbourne, C., Hayes, R.D., et al. “Summary and Discussion of MOS Measures,” in A.L. Stewart & J.E. Ware (eds.), Measuring Functioning and Well-Being: The Medical Outcome Study Approach (pp. 345-371). Durham, NC: Duke University Press, 1992. | | | | | | | | | | | | | | | | | | | | | | | | | | |

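### The SF-36 missing-item rule in Appendix 6 sets no minimum number of answered items and does not say whose average is used

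*Protocol*

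**What the plan says.** SF-36 is a secondary efficacy indicator (Protocol 8.2), scheduled at all six time points t0 to t5 (Appendix 2, Table 1). Scoring is fixed in Appendix 6, Table 5.

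- Conversion to a 0 to 100 scale: "Score conversion = (actual score - lowest score in that aspect) / (highest score in that aspect - lowest score in that aspect) × 100".
- Missing items, in the same row: "missing entry scores are replaced by the average score of their respective aspect".
- The longest domain: "Physical Functioning(PF), Consist of items 3-12", with "PF=(actual score-10）/20×100". Each item scores 1, 2 or 3.
- Item 22 has its own alternative scoring line, labelled "Unanswered items 21", for use when item 21 is blank. The form therefore expects that some items will be left unanswered.

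Elsewhere, section 11.1.2(4) says "For unexamined items, it must be marked as" ND. Section 11.2.1 says "The statistical analysis will use intention-to-treat (ITT) for missing data", which concerns analysis populations and not questionnaire items. No section gives a completeness threshold for an SF-36 domain, and none defines the average.

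**The concern.** Replacing a blank item by a domain average is reasonable when most of the domain was answered. With no floor, the same sentence also applies when almost nothing was answered. The Physical Functioning items run from vigorous activity to bathing or dressing, so a score built on one or two of them depends mainly on which ones were answered. The rule also covers every missing entry without exception, yet it cannot be carried out from the patient's own data when the whole domain is blank. At that point two programmers could do different things: leave the score missing, or borrow an average from other patients.

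At stake is the meaning of some domain scores on a secondary outcome in groups of 22. Because the Protocol prints an operative rule, this is not simply a detail left to a statistical analysis plan. A later plan could add a floor, but it would be adding a limit that the score sheet does not contain.

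**Working it through.** **Inputs.** All come from Appendix 6, Table 5: ten Physical Functioning (PF) items scored 1 to 3, three Role-Emotional (RE) items scored 1 or 2, their conversion formulas, and the missing-item sentence. The average is read here as the patient's own, which is the natural reading on a one-patient form.

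**Reproducing the printed formula.** Ten items scored 1 to 3 give a lowest sum of 10, a highest of 30 and a span of 20. The printed PF constants (10 and 20) agree, and PF runs from 0 to 100. RE has a lowest sum of 3, a highest of 6 and a span of 3, which also agrees.

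**One item answered.** The other items take the same value.

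- PF, answer v: (10v − 10)/20 × 100. For v = 1, 2, 3 this is 0, 50, 100.
- RE, answer v: (3v − 3)/3 × 100. For v = 1, 2 this is 0, 100.

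**Illustrative patient.** Suppose that items 3 to 12 would truly be answered 1, 1, 2, 1, 2, 1, 1, 2, 3, 3.

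- All ten answered: sum 17, PF = (17 − 10)/20 × 100 = 35.
- Only item 3 answered (1): filled sum 10, PF = 0.
- Only items 11 and 12 answered (3, 3): filled sum 30, PF = 100.

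**k of ten PF items answered.** The filled score can take 2k + 1 values. The worst case is every answered item at 3 and every missing item truly at 1. The filled score is then 100 and the true score is (3k + (10 − k) − 10)/20 × 100 = 10k, so the error is 100 − 10k.

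| Items answered | Attainable scores | Worst-case error (points) |
|---|---|---|
| 1 | 3 | 90 |
| 5 | 11 | 50 |
| 9 | 19 | 10 |
| 10 | 21 | 0 |

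**Typical rather than worst-case error.** This needs assumptions that the Protocol does not supply: ten equally difficult three-level items, latent inter-item correlation 0.3 to 0.7, and items missing at random. Under these, simulation gives a root-mean-square error against the full PF score of about 25 to 34 points with one item answered, 8 to 11 with five, and 3 to 4 with nine.

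**No item answered.** The patient's own mean is 0/0, so no score can be formed. The same holds for health transition, which consists of item 2 alone. Only an average over other patients would satisfy the sentence literally, and the text does not call for one.

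**Effect of a half-items floor on the same patient.** With exactly five items answered, PF could be as low as 0 (items 3, 4, 6, 8, 9, all 1) or as high as 70 (items 5, 7, 10, 11, 12: sum 12, mean 2.4, filled sum 24, PF = 14/20 × 100). The floor narrows the error but does not remove it.

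**The case against.** The strongest reply is that the situation should rarely arise. Section 14.1 requires every CRF item to be completed, section 14.2 has omissions checked and monitored, and section 14.4 assigns one researcher to complete the SF-36 assessment. One answered item out of ten is an edge case under those arrangements. A completeness floor is also a scoring detail that a statistical analysis plan could supply, and half is only one possible threshold. All of this stands and limits the weight of the point. It does not repair the sentence, because completion instructions are not scoring rules and the form itself provides for blanks.

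Several stronger readings are tempting, and the Protocol does not support them.

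- A reader might infer that a wholly unanswered domain still receives a full score. On the natural reading it receives none. The defect is that the rule does not say so.
- A reader might infer an inflated type I error or a diluted group difference. That would need other patients' averages to be used and whole blocks to be skipped at some rate. The Protocol states neither.
- A reader might infer that filled scores are analysed as if observed. No section says this. Section 11.1.2 requires derived results to be traceable to the original data, section 14.3 keeps the original scales, and Appendix 2 lists an analysis of missing items at t5, although it does not describe it.
- A reader might see a conflict with ND marking. An item can be marked ND while the domain score is calculated in its own column.

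**Conclusion.** The point holds and is minor. The Protocol fixes a replacement rule that has no floor, does not define its average, and is undefined when nothing in a domain was answered. In the extreme case a PF score moves from 35 to 0 or 100 according to which items were answered, and RE from a single item can only be 0 or 100. These are properties of the rule as written. How often they would matter cannot be known, because the Protocol gives no item non-response rate. If few items are skipped the effect is small, and the completion and monitoring provisions make heavy loss unlikely.

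The conclusion does not extend to every domain reaching 100. As printed, the Mental Health formula multiplies by 10 and so stops at 10, and the Social Functioning formula divides by 9 against a true span of 8 and so stops at 88.9. Those are separate errors that apply even to complete questionnaires.

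**What to change.** Replace the missing-item sentence in Appendix 6 with wording to this effect:

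*An unanswered item stays marked ND. For scoring, it is replaced by the mean of the same patient's answered items in the same domain at the same visit, only if at least half of that domain's items were answered. Otherwise the domain score is missing at that visit. Answers from other patients are never used.*

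The half threshold is a proposal. The sponsor may choose another, provided that it is stated before scoring. At half, PF needs five of ten items and RE two of three, and health transition is missing when item 2 is blank. For PF the worst-case error falls from 90 to 50 points. Keep the separate scoring line for item 22 when item 21 is unanswered.

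The cost is one sentence in the appendix and a line in the scoring program. The only downside is that a few domain scores become missing instead of being filled in.

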**Appendix 7 Table 6 Randomization Application Form**

Application Date: Year Month Day Random Number:

| **General Information** | | | |
| --- | --- | --- | --- |
| Name Abbreviation: | | Age: years | Gender: Male □ Female □ |
| Weight： Kg | | Height： m | BMI Index： Kg/m2 |
| DMS-5 Diagnosis | Generalized Anxiety Disorder Severity: Mild □, Moderate □, Severe □ | | |
|  | Severity of Major Depression: Mild □, Moderate □, Severe □ | | |

| Selection Criteria Checklist | | |
| --- | --- | --- |
| Inclusion criteria | Yes | No |
| 1.Meeting the CPPS diagnostic criteria in the 2022 EAU guidelines | □ | □ |
| 2. Definitive generalized anxiety disorder or major depressive disorder | □ | □ |
| 3. Individuals aged between 18 and 70 years | □ | □ |
| 4.No identifiable pathological changes in physical examinations and auxiliary tests | □ | □ |
| 5.No treatment other than oral medications in the 3 months prior to the visit | □ | □ |
| 6.Patient's informed consent and voluntary participation in the study | □ | □ |
| All of the above criteria must be "yes," otherwise the patient cannot be enrolled. | | |

| Exclusion Criteria Checklist | | |
| --- | --- | --- |
| Exclusion criteria | Yes | No |
| 1. Patients in the acute phase of systemic and intracranial hemorrhagic diseases | □ | □ |
| 2.Individuals with serious underlying conditions, such as cardiovascular, liver, kidney, respiratory, and blood disorders, in addition to malignant tumors and other advancing illnesses | □ | □ |
| 3.Patients with cardiac metal membranes, cardiac pacemakers, intracranial metal implants, lumbar sacral metal implants, and implantable electronic devices | □ | □ |
| 4.Individuals with infections in the head or lumbar sacral regions | □ | □ |
| 5.Individuals exhibiting unstable vital signs | □ | □ |
| 6.Patients with previous adverse reactions to magnetic therapy | □ | □ |
| 7.Individuals with atypical autonomic reflexes | □ | □ |
| 8. Patients with cognitive impairment who cannot cooperate | □ | □ |
| 9. Expectant or breastfeeding women | □ | □ |
| 10. Patients with a history diseases causing peripheral nerve damage | □ | □ |
| 11. Patients with debilitating diseases, such as malignant effusion, active pulmonary tuberculosis, cancer, or myasthenia gravis | □ | □ |
| 12.Patients with severe mental illness or epilepsy | □ | □ |
| All of the above criteria must be "no"; otherwise, the patient cannot be enrolled. | | |

Is it eligible for enrollment: Yes □ No □

Reason for not enrolling:

Randomization results for eligible participants:

Group A (dual-target magnetic stimulation) □

Group B (peripheral magnetic stimulation) □

Group C (sham stimulation) □

**Thank you for your participation!**
